### Secondary variables

4.15

#### Lower limb functionality

4.15.1

Lower limb functional performance will be assessed using the Timed Up and Go (TUG) test, a well-established measure of functional mobility and dynamic postural control in adult populations (65, 66). The test records the time (in seconds) required for participants to rise from a seated position, walk three meters at a comfortable pace, turn, return to the chair, and sit down. The TUG demonstrates excellent test–retest reliability (intraclass correlation coefficient >0.95) and strong concurrent validity with other indicators of mobility and functional balance across different age groups (67). Longer completion times reflect poorer functional mobility and dynamic balance. Results will be interpreted using age- and sex-specific normative reference values for adults (68).

#### Lower limb flexibility

4.15.2

Flexibility of the lower limbs will be evaluated using the modified seated reach test, which estimates extensibility of the posterior muscular chain, particularly the hamstrings and lumbar region, in adults. Participants will sit on a standard chair with one foot flat on the floor and the contralateral leg extended forward, heel in contact with the ground. With the extended knee maintained in full extension, participants will slowly lean forward and reach as far as possible with both arms. Reach distance will be measured in centimeters from a fixed reference point at the toes (69). One familiarization trial will be performed, followed by two valid attempts, with the best value retained for analysis.

#### Blood pressure

4.15.3

Resting blood pressure will be measured using a validated automatic digital sphygmomanometer for the assessment of systolic and diastolic blood pressure in adults (70). Measurements will be obtained with participants seated, the arm supported at heart level, and after a minimum of five minutes of rest, in accordance with American Heart Association guidelines for standardized blood pressure assessment (71). Two measurements will be recorded, one immediately before the training session and one at its conclusion, using identical procedures for both study groups.

#### Metabolic health

4.15.4

Metabolic health will be evaluated through the assessment of glycosylated hemoglobin (HbA1c), lipid profile parameters, and other routinely used biochemical markers indicative of glycemic control and cardiovascular risk in adults (72, 73).

Venous blood samples will be collected by certified phlebotomists at an accredited clinical laboratory following standardized pre-analytical procedures. All samples will be obtained in the morning after an overnight fasting period of 8–12 h and processed according to established laboratory protocols. Analyses will be performed using validated automated systems, with internal quality control procedures ensuring analytical accuracy and reproducibility.

HbA1c will be measured from venous blood samples using methods standardized by the National Glycohemoglobin Standardization Program (NGSP) and traceable to the Diabetes Control and Complications Trial (DCCT). Results will be expressed as percentages (%). HbA1c values ≥5.7% will be interpreted as impaired glucose regulation, while values ≥6.5% will be considered diagnostic of diabetes mellitus, in accordance with American Diabetes Association (ADA) criteria (74).

The lipid profile will include total cholesterol, high-density lipoprotein (HDL) cholesterol, low-density lipoprotein (LDL) cholesterol, and triglycerides, measured using enzymatic colorimetric methods. LDL cholesterol will be calculated or directly measured according to laboratory standards. Results will be interpreted in accordance with the clinical recommendations of the European Society of Cardiology and the European Atherosclerosis Society (73).

#### Physical activity level

4.15.5

The International Physical Activity Questionnaire (IPAQ) short form will be employed to evaluate physical activity, providing a standardized method to measure the frequency, duration, and intensity of activities performed in the preceding seven days. The IPAQ demonstrates sufficient validity and reliability in assessing physical activity in adult populations within both clinical and community settings (75). Weekly energy expenditure will be measured and expressed in metabolic equivalent minutes per week (MET-min/week), calculated from the duration of vigorous-intensity activity, moderate-intensity activity, and walking. Participants will be categorized into low, moderate, or high physical activity levels according to the criteria established by the questionnaire developers (76).

#### Body composition

4.15.6

Body composition will be assessed using bioelectrical impedance analysis with the InBody 270 device (InBody Co., Ltd., South Korea). This method quantifies fat mass, fat-free mass, and total body water through the analysis of body resistance and reactance via a low-intensity alternating electrical current (77).

#### Quality of life

4.15.7

The World Health Organization Quality of Life–BREF questionnaire (WHOQOL-BREF) will be employed to evaluate individuals’ self-reported well-being across many aspects. This measure will be employed to assess health-related quality of life. The WHOQOL-BREF exhibits robust reliability and validity in adult populations across many sociocultural situations (78). The questionnaire consists of 26 items divided into four domains: physical health, psychological well-being, social relationships, and environmental context, in addition to two general items evaluating perceived health status and overall quality of life. Responses are evaluated using a five-point Likert scale, with higher scores signifying an improved subjective quality of life. Domain scores are normalized to a 0–100 scale to facilitate comparisons across domains and populations (79).

#### Motivation for physical exercise

4.15.8

The Behavioral Regulation in Exercise Questionnaire–3 (BREQ-3) (80, 81) will be employed to evaluate motivation for physical exercise. This instrument is based on self-determination theory and is designed to capture various forms of motivational regulation that influence exercise adherence. In adult and physically active populations, the BREQ-3 has exhibited cross-cultural validity and sound psychometric properties (82). The questionnaire comprises 24 items that are organized into six subscales that represent varying degrees of self-determination: amotivation, external regulation, introjected regulation, identified regulation, integrated regulation, and intrinsic motivation. Scores are determined on a five-point Likert scale, with a score of 0 indicating “not at all true for me” and a score of 4 indicating “completely true for me.” Higher scores indicate a higher degree of autonomous motivation. The Relative Self-Determination Index (SDI) can be used to summarize outcomes or to analyze them at the subscale level, as it represents the motivational continuum described by the theory (83).

#### Barriers and benefits of physical exercise

4.15.9

The Exercise Benefits/Barriers Scale (EBBS), a validated instrument, will be employed to evaluate the perceived advantages and obstacles of physical exercise, with a particular emphasis on the psychosocial factors that influence regular physical activity participation. The EBBS demonstrates robust psychometric qualities, including outstanding internal consistency and construct validity, across a variety of adult populations. The scale is composed of 43 items that are categorized into two dimensions: perceived benefits (29 items) and perceived barriers (14 items) that are associated with physical activity (84, 85).

#### Sociodemographic variables and lifestyles

4.15.10

Participants’ sociodemographic characteristics, including age, residential area (urban or rural), schooling completed (primary: <8 years; secondary: 8–12 years; additionally higher education: >12 years), and the presence of chronic conditions such as hypertension, diabetes mellitus, and dyslipidemia, will be collected. Additionally, lifestyle behaviors, including tobacco consumption and alcohol consumption, will be recorded. Additionally, concise surveys will be implemented to assess sleep patterns and dietary habits. All questionnaires and functional assessment tools used in this protocol have demonstrated acceptable validity and reliability in Chilean adult populations.

### Statistical analysis

4.16

Multiple imputation methods will be employed to address missing data in accordance with the intention-to-treat principle (86). Descriptive statistics for continuous variables will be presented using measures of central tendency and dispersion, whereas categorical variables will be represented through frequencies and percentages. The Shapiro–Wilk test assesses data distribution, whereas Levene’s test evaluates the homogeneity of variances.

Non-parametric sensitivity analyses will be conducted when the criteria for normality or homoscedasticity are not met, due to the limited sample size (*n* = 22) and potential violations of parametric assumptions. Wilcoxon signed-rank tests will be used for within-group comparisons, while Mann–Whitney U tests will be applied for between-group comparisons.

A two-way repeated-measures analysis of variance (ANOVA) will be conducted to assess intervention effects, incorporating group (experimental vs. control), time (pre-intervention vs. post-intervention), and the group × time interaction as model factors. Bonferroni-adjusted *post hoc* tests will be utilized where necessary to determine statistically significant differences. Effect sizes will be computed utilizing Cohen’s d and classified as inconsequential (<0.20), small (0.20–0.49), moderate (0.50–0.79), or large (≥0.80) (87). Statistical analyses will be performed utilizing SPSS software (version 25; IBM Corp., Chicago, IL, USA), with a significance threshold established at *p* < 0.05. Graphical analyses will be conducted with GraphPad Prism (version 8, GraphPad Software, San Diego, CA, USA).

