### Sample size

4.3

The sample size was determined *a priori* using G*Power software (version 3.1.9.7, Heinrich Heine University Düsseldorf, Düsseldorf, Germany) for a pre–post intervention comparison of mean differences. Based on an anticipated effect size of 0.8 for aerobic capacity, derived from previously published data (29), a minimum of 16 participants (eight per group) was required to achieve a statistical power of 80% (1 − *β* = 0.80) with a two-sided significance level of *α* = 0.05. To account for potential attrition, an additional six participants will be recruited, resulting in a total sample of 22 individuals (11 per group; Figure 1).

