### Randomization

4.5

Eligible participants will be randomly allocated to study groups following completion of baseline assessments. The randomization sequence will be generated using computer-based random number software by a co-investigator who is independent of participant recruitment and assessment procedures. Stratified randomization based on age and body weight will be applied, using permuted blocks of variable size to ensure balanced group allocation.

Allocation concealment will be maintained through the use of sequentially numbered, opaque, sealed envelopes prepared in advance by the co-investigator responsible for the randomization sequence. Envelopes will be opened only after participants have completed all baseline evaluations. Participants will then be assigned to one of two study arms: “G1” the Fit-Folk Cardiovascular Dance (FCD) group, which will receive the culturally adapted dance-based intervention, or “G2” the Conventional Physical Exercise (CPE) group, which will follow a standard exercise program.

Outcome assessors will remain blinded to group allocation. All evaluations will be conducted by personnel not involved in intervention delivery, following standardized scripts, and in separate facilities and schedules to prevent contact with intervention activities. Participants will be instructed not to disclose their group assignment during assessments. The statistical analyst will also remain blinded: an independent investigator will recode the dataset into ‘Group A’ and ‘Group B’ prior to analysis, and unblinding will occur only after completion of the primary analyses. Due to the behavioral nature of the interventions, participants cannot be blinded to their assigned program; however, this does not compromise the blinding of assessors or analysts.

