### Analysis variables

4.13

In both study arms, assessments will be conducted at baseline and post-intervention to evaluate physical health parameters, health-related quality of life, motivation for physical activity, and perceived barriers to and benefits of exercise. Data will be collected using standardized case report forms and subsequently entered into a secure database incorporating quality control procedures, including range checks and automated alerts for missing or inconsistent values. All assessments will be performed by qualified health professionals who will remain blinded to group allocation. Prior to study initiation, outcome assessors will receive structured training to standardize measurement procedures and ensure consistent application of assessment protocols, thereby enhancing reliability and minimizing measurement bias (56).

All assessment activities will take place at the Huichacura-Cayuqueo community center, following a scheduled appointment system and in a facility designed to ensure participant privacy and appropriate environmental conditions, including controlled temperature and humidity. Blood samples will be collected and analyzed at an accredited laboratory within the municipality of Padre Las Casas, in accordance with institutional procedures. Participants will be instructed to observe a fasting period of at least 8 h and no more than 12 h prior to blood collection to ensure analytical accuracy.

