#### Cardiorespiratory capacity

4.14.1

Cardiorespiratory fitness will be the primary outcome of the trial and will be assessed using the 3 × 1 Step Test (ST3 × 1), a validated protocol for estimating VO₂max in adults with cardiovascular risk factors (57). During the test, participants will repeatedly step up and down from a standardized platform (0.20 m in height) across three progressively demanding 1-min stages, each separated by a 1-min recovery period. Heart rate and blood pressure will be measured immediately upon test completion and again after one minute of recovery.

Test-derived estimates will be recorded and interpreted using age- and sex-specific normative reference values. Results falling below the established percentile thresholds will be classified as indicative of diminished cardiorespiratory fitness (58).

To ensure participant safety during the 3 × 1 Step Test, trained evaluators will monitor blood pressure and heart rate before the test, conduct continuous observation for signs of exercise intolerance during the protocol, and repeat cardiovascular measurements immediately after completion and during the recovery period. The test will be discontinued if any adverse symptoms occur, and participants exhibiting abnormal responses will be referred for clinical evaluation.

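### The repeated-measures ANOVA neither conditions on baseline nor uses the stratifiers (age, body weight): a valid analysis, but usually less precise than baseline-adjusted ANCOVA

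*Protocol article*

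**What the plan says.** - **Outcome and timing.** Section 4.14.1 states: "Cardiorespiratory fitness will be the primary outcome of the trial". It is measured by a step test that estimates VO₂max. Section 4.13 sets two measurement times: "assessments will be conducted at baseline and post-intervention".
- **Model.** Section 4.16 names one model for intervention effects, a two-way repeated-measures ANOVA, "incorporating group (experimental vs. control), time (pre-intervention vs. post-intervention), and the group × time interaction as model factors". Baseline enters only as one level of the time factor. No covariate is listed.
- **Rank tests.** The same section adds, as sensitivity analyses when normality or equal variance fails: "Wilcoxon signed-rank tests will be used for within-group comparisons, while Mann–Whitney U tests will be applied for between-group comparisons". These are also unadjusted.
- **Design.** Section 4.5 states: "Stratified randomization based on age and body weight will be applied". Envelopes are opened only after all baseline evaluations, so baseline fitness, age and weight are known before allocation. The statistical section does not mention the stratifiers.

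**The concern.** The trial has 22 women, and baseline fitness is a free source of precision. The planned model does not use it well. A change score subtracts the whole baseline difference between arms, whereas only the part that carries through to the post-intervention value (a fraction r) should be removed. With r below 1 the change score therefore over-corrects any chance imbalance. ANCOVA estimates the right fraction from the data.

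The stratifiers raise a second question. Balancing on age and weight reduces the true variability of the arm comparison if these factors are prognostic. A model without them does not credit that reduction, so its standard error is too large.

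The three-term model also offers more than one result that could be called an intervention effect. Only the interaction compares the arms on change. The group term averages in the pre-treatment value, and the time term is not a comparison between arms.

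**Working it through.** **Inputs from the protocol article.** Two arms of 11 (N = 22), two time points, two-sided α = 0.05, effect size 0.8 and target power 80% (section 4.3); model terms (section 4.16); stratifiers (section 4.5).

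**Assumptions, because the documents give no figure.** The pre-post correlation r is varied from 0.3 to 0.9. The between-arm difference is taken as 0.8 outcome SD. The outcome SD σ is set to 1 at both times.

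**1. The plan's own figure.** Section 4.3 describes a "pre–post intervention comparison of mean differences" and needs 16 women.
- A paired t-test with d = 0.8 needs 15 in total (power 82%), or 16 when made even.
- A group × time test with Cohen's f = 0.4 and r = 0.5 has noncentrality 0.4² × 16 × 2/(1 − 0.5) = 10.24. It gives N = 16 with power 84.5%.
- A two-arm comparison with d = 0.8 needs 26 per arm, so it does not reproduce 16. At 11 per arm its power is 43%.

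**2. What the planned test is.** With two time points, the group × time F test equals the two-sample t-test on change scores, with N − 2 = 20 df. Its variance is 2(1 − r) × 2/11.

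**3. ANCOVA on baseline alone.** The variance is (1 − r²) × 2/11 × [1 + 1/(N − 4)], with 19 df. The bracket is the cost of estimating one slope: 1 + 1/18 = 1.056. The variance ratio to the plan is (1 + r)/2 × 1.056.

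**4. ANCOVA on baseline, age and weight, when age and weight add nothing beyond baseline.** The bracket becomes 1 + 3/16 = 1.19, with 17 df. No credit is given for stratified balance, so this is the unfavourable end of the range.

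| r | Variance ratio, baseline only | Power, planned | Power, baseline only | Power, full model, no added prognostic value |
|---|---|---|---|---|
| 0.3 | 0.69 | 33% | 44% | 40% |
| 0.5 | 0.79 | 43% | 52% | 47% |
| 0.7 | 0.90 | 64% | 68% | 62% |
| 0.8 | 0.95 | 81% | 82% | 77% |
| 0.9 | 1.00 | 98% | 98% | 96% |

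Simulation at 11 per arm agrees to within about one percentage point.

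Example at r = 0.5: the planned variance is 2 × 0.5 × 2/11 = 0.182 and the ANCOVA variance is 0.75 × 2/11 × 1.056 = 0.144. Since 22/0.79 ≈ 28, 22 women under ANCOVA are worth about 28 under the plan.

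Break-even for baseline-only ANCOVA: (1 + r)/2 × 1.056 = 1 gives r ≈ 0.89. For the full model with uninformative stratifiers: (1 + r)/2 × 1.19 = 1 gives r ≈ 0.68.

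**5. When the stratifiers do carry information.** These are simulations at N = 22 with stratified allocation and r = 0.5. They show the power of baseline-only ANCOVA and then of the model with continuous age and weight:
- none of the residual variance explained: 53% to 50%;
- 10% explained: 52% to 53%;
- 25% explained: 51% to 60%.

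At r = 0.7 with 25% explained, type I error was 3.6% for the planned test and 5.0% with the stratifiers in the model. Leaving them out is therefore conservative.

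**The case against.** The strongest case for the plan has four parts.

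- **The interaction test is valid.** Under randomisation it is unbiased. This stands: the loss is of precision only.
- **ANCOVA is not always better at this size.** A reader might infer from the large-sample ratio (1 + r)/2 that it wins at any correlation below 1. At N = 22 the gain is gone near r = 0.9. Once age and weight are added without prognostic value, it is gone by about r = 0.7. This stands, and it limits the size of the claim.
- **Constant effects of age and weight already cancel.** A change score removes any effect of the stratifiers that is the same at both times. Omitting them matters only if they predict change. This also stands, so the gain in power from including them is conditional.
- **Some of this may be settled elsewhere.** Section 4.1 says that a comprehensive analysis plan is public, and it is not shown here. It may name the deciding term or add covariates. But section 4.16 writes the model out, so the point concerns a stated choice.

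A reader might also infer that the plan will treat significance in one arm only as a treatment effect. If both arms truly improved by 0.8 SD of change, each within-arm paired test would have power 0.668 at n = 11, and the two would disagree in 2 × 0.668 × 0.332 = 44% of trials. The document does not plan that reading. It ties only the rank tests to assumption failure and labels them sensitivity analyses, while the Bonferroni post hoc tests are not tied to the assumption checks. The 44% describes a possible misuse.

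**Conclusion.** The concern holds as a moderate and inexpensive improvement. The stated model leaves baseline out as a covariate and does not carry the stratifiers into the analysis.

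For a 0.8 SD difference at 11 per arm, baseline adjustment adds about 12 power points at r = 0.3, 9 at 0.5, 4 to 5 at 0.7, 2 at 0.8 and none at 0.9. All of these rest on an assumed r and an assumed between-arm effect.

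The case for adding age and weight is mainly that the analysis should match the stratified randomisation and give a correct standard error. Whether they also add power depends on their prognostic value, which the documents do not give.

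The documents do not support a claim that the planned test is biased or invalid. Nor does ANCOVA rescue the sample size: a between-arm effect of 0.8 SD remains underpowered at moderate r under either analysis.

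**What to change.** In section 4.16:

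1. Make the primary test the arm coefficient, with its 95% CI, from a linear model of post-intervention estimated VO₂max on arm and baseline VO₂max.
2. Include age and body weight as continuous terms in that model. Fix this choice before unblinding, and acknowledge that it may cost power if they are not prognostic.
3. Use the same form, with the outcome's own baseline, for the continuous secondary outcomes.
4. Report within-arm changes descriptively, and state that they are not evidence of a difference between arms.

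**Cost.** The change is to wording only, since every covariate is measured before allocation. Baseline alone uses one degree of freedom (20 to 19) and inflates the variance by 1/18, about 6%. All three covariates use three (20 to 17; t critical value 2.09 to 2.11) and inflate it by about 3/16, or 19%, before any gain from what they explain. If age and weight explain nothing beyond baseline, the two terms cost about 2 to 5 power points. The sample-size basis in section 4.3 needs separate attention.

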**Results:**

The culturally customized intervention is anticipated to yield increased levels of emotional well-being, perceived self-efficacy, and adherence in comparison to conventional exercise. The incorporation of Mapuche cultural elements, particularly traditional dancing, has the potential to enhance physical health, foster social engagement, reinforce cultural identity, and enhance community engagement.

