## Research question

2

Is a culturally adapted cardiovascular dance program (Fitfolk) as effective as, or more effective than, a conventional physical exercise program in improving physical health, health-related quality of life, and exercise motivation, and in reducing perceived barriers to physical activity among rural Indigenous women with overweight or obesity and cardiometabolic risk in the commune of Padre Las Casas, Chile?

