Notably, even without statistically significant metabolic effects, the results of this study would offer important insights into the function and constraints of cultural elements in exercise-based therapies. These results may suggest that metabolic outcomes are more significantly affected by training volume and intensity than by cultural adaptation alone, or that extended intervention durations and greater community engagement are necessary to produce substantial physiological changes.

This protocol is characterized by its incorporation of stringent quantitative methods within an intercultural framework, targeting a population that has been traditionally marginalized in clinical research. The study enhances the acknowledgment of Indigenous views in health research by including Mapuche women and appreciating traditional knowledge in the intervention design. The findings may guide the formulation of intercultural health policies and community-based initiatives that integrate Indigenous identity as a fundamental element of preventive and treatment approaches.

Expected limitations encompass difficulties in maintaining long-term compliance, potential selection bias, and logistical obstacles associated with doing research in rural community environments. The study aims to produce evidence that endorses the creation of culturally customized intervention models for obesity management and enhances the cultural significance of physical and mental health promotion programs within Indigenous groups.

This protocol presents a novel, comprehensive, and culturally attuned method for addressing obesity in Mapuche women. This approach integrates scientific evidence with sociocultural context to produce transferable and socially relevant knowledge consistent with intercultural health principles, while offering a solid clinical framework to inform future interventions in Indigenous communities.

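### One p < 0.05 threshold covers 20 to 28 secondary measures with no stated adjustment or order, while the research question asks about effectiveness in three domains that hold only secondary outcomes.

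*Protocol article*

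**What the plan says.** The Methods part of the abstract and section 4.14.1 name cardiorespiratory fitness (the 3 × 1 step test) as the primary outcome. Section 4.15 is headed as secondary variables. The sample size rests on the same primary: "Based on an anticipated effect size of 0.8 for aerobic capacity", "with a two-sided significance level of" 0.05.

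Section 4.16 tests intervention effects with a two-way repeated-measures ANOVA (group, time, group × time), "with a significance threshold established at" p < 0.05. The only adjustment it names is Bonferroni for post hoc tests, to be used where needed. It does not say that this runs across outcomes, gives no order among the secondary outcomes and does not call them exploratory.

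The research question (section 2) asks whether Fit-Folk matches or exceeds conventional exercise "in improving physical health, health-related quality of life, and exercise motivation, and in reducing perceived barriers to physical activity". It does not mention the primary outcome by name.

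**The concern.** The primary outcome belongs to one of the four domains in the research question, physical health. The other three (quality of life, motivation, barriers) can be answered only with secondary outcomes. Under section 4.16, each of these is judged at the same p < 0.05 as the primary.

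If the primary result is null, one or more nominally significant secondary results can easily arise by chance. Nothing in this article stops such a result from being read as an answer to the research question in its domain. With 11 women per arm, an isolated chance finding would also carry a large apparent effect.

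**Working it through.** **The plan's own figures.** The article states no family-wise error rate, so there is none to reproduce. Its sample size reads "a minimum of 16 participants (eight per group) was required to achieve a statistical power of 80"%, raised to 22 (11 per group). N = 16 is reproduced as a group × time interaction with f = 0.4 and an assumed pre-post correlation of 0.5: power is 0.785 at N = 14 and 0.845 at N = 16. The calculation covers aerobic capacity only. This point takes from it the 11 per arm.

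**Counting the secondary measures (sections 4.15.1 to 4.15.9).**

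| Measure | Tests |
|---|---|
| Timed Up and Go | 1 |
| Seated reach | 1 |
| Systolic and diastolic pressure | 2 |
| HbA1c | 1 |
| Lipids | 4 |
| IPAQ, MET-min/week | 1 |
| Body composition | 3 |
| WHOQOL-BREF domains | 4 |
| BREQ-3 subscales | 6 |
| EBBS dimensions | 2 |
| **Total** | **25** |

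- Lower count: section 4.15.8 allows BREQ-3 to be summarised by one index instead of six subscales: 25 − 6 + 1 = 20.
- Higher count: the two WHOQOL-BREF general items and the BREQ-3 index alongside its subscales: 25 + 2 + 1 = 28.
- Not counted: the unspecified further biochemical markers in 4.15.4, and the two strength tests, which stand under the main variables in 4.14.

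**Reach of the Bonferroni step.** Group and time have two levels each, so each factor has a single pairwise contrast. Read as a post hoc correction within one ANOVA, Bonferroni can act on a few simple effects of one outcome and does nothing across outcomes.

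**Chance of a false result, independent outcomes.** With k true-null tests at two-sided 0.05:

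- any p < 0.05 in either direction: 1 − 0.95^k. For k = 25: 1 − 0.95^25 = 0.72.
- at least one result favouring Fit-Folk: 1 − 0.975^k. For k = 25: 1 − 0.975^25 = 0.47.
- expected number of false positives in either direction: 25 × 0.05 = 1.25, of which 25 × 0.025 = 0.625 favour Fit-Folk. These averages do not depend on correlation.

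**Chance of a false result, correlated outcomes.** Lipids, body-composition measures and questionnaire subscales are correlated, and the article gives no correlations, so these are assumed. Null trials were simulated with 11 per arm and two-sample t tests on equally correlated change scores, which is equivalent to the group × time test. Outcomes were scored so that higher is better.

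| Tests | Assumed correlation | Any p < 0.05 | Favouring Fit-Folk |
|---|---|---|---|
| 25 | 0 | 0.72 | 0.46 to 0.47 |
| 25 | 0.3 | 0.62 | 0.33 |
| 25 | 0.5 | 0.48 | 0.25 |
| 25 | 0.8 | 0.26 | 0.13 |
| 20 | 0.5 | 0.43 | 0.22 |

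Repeat runs differ by about 0.01. If correlation is instead set by instrument (0.5 to 0.7 within, 0.1 to 0.3 between), 25 tests give 0.55 to 0.66 for any false positive and 0.29 to 0.38 for one favouring Fit-Folk.

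**The case against.** The strongest reply has four parts.

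1. **The article does rank its outcomes.** It names one primary, sizes the trial on it and labels section 4.15 secondary. This stands. A reader might infer that there is no hierarchy or that all outcomes have equal rank, and the text does not support that. What is missing is an order or adjustment among the secondary outcomes, and a research question that reflects the ranking.

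2. **Secondary multiplicity is commonly left to the statistical analysis plan.** Section 4.1 says that plan is public, and it is not shown here. This stands as far as silence goes. But the article states a blanket threshold, and the mismatch between the named primary and the research question is in its own text, which a separate plan would not remove.

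3. **Nothing says that one significant secondary result will be claimed as benefit.** This also stands. The abstract's expectation ("anticipated to yield increased levels of emotional well-being, perceived self-efficacy, and adherence in comparison to conventional exercise") might be read as such a plan, but it names constructs rather than a decision rule: adherence is not a 4.15 outcome, and no listed instrument measures self-efficacy. The Discussion's remark that "even without statistically significant metabolic effects, the results of this study would offer important insights" concerns how a null metabolic result would be interpreted.

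4. **The size is easily overstated.** A reader might infer from the 48% that a false claim of benefit is about as likely as not. That figure includes false results favouring conventional exercise. In the dance arm's favour it is about 25% at the same correlation, and it approaches one half only for independent outcomes. Nor does the article state a family-wise 0.05 against which a multiple could be quoted.

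**Conclusion.** The point holds in a limited form. The primary test is sound in this respect. The weakness is that p < 0.05 applies unprotected to 20 to 28 secondary measures, while the research question asks about effectiveness in domains that only those measures can answer.

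For 25 tests with no true arm difference on any of them, a false significant difference in one direction or the other has a chance of about 48%, and a false result favouring Fit-Folk about 25%. Both rest on an assumed common correlation of 0.5. Over correlations from 0.8 to 0 they run from 26% to 72% and from 13% to 46 or 47%. They count one deciding test per outcome, the group × time interaction. The counts, the single threshold and the wording of the research question come directly from the article. The correlations do not.

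**What to change.** In section 4.16, state that the confirmatory p < 0.05 claim applies only to cardiorespiratory fitness. State that the 4.15 outcomes are supportive or exploratory, reported as between-group differences with 95% confidence intervals and without claims of effectiveness. Reword the research question so that effectiveness refers to the primary outcome and the other domains are described as secondary.

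Holm or fixed-order testing of one named measure per domain is optional if a formal claim there is wanted. Bonferroni across all 25 would be impractical: 0.05/25 = 0.002 per test leaves about 8% power for a standardised difference of 0.8 with 11 per arm.

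The cost is wording only, with no extra data or design change. The downside is that isolated significant secondary results can no longer be presented as proof of effect.
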